#### Exploratory aims:

To estimate the costs of different implementation interventions and determine the incremental cost-effectiveness of added coaching and/or facilitation.To assess whether the effect of augmenting REP with coaching or facilitation is moderated by SP or school factors such as SP knowledge and perceptions of CBT as well as school administrator support of CBT implementation.To determine whether coaching and facilitation improve CBT knowledge, perceptions, skills, or championing skills among SPs, and which of these account for increases in frequency of CBT delivery and improvement in student clinical symptoms.

### Methods

This study employs a clustered, sequential multiple assignment randomized trial (SMART) design to inform development of an adaptive implementation intervention (Fig. 1). The study was reviewed and approved by the University of Michigan Institutional Review Board (IRB; UM Protocol # HUM00132239). The study takes advantage of an ongoing initiative to disseminate CBT training in schools in the State of Michigan, the Transforming Research into Action to Improve the Lives of Students (TRAILS) program. All program delivery, training, and implementation support is provided through TRAILS and is considered non-research per local IRBs, and considered exempt from regulation under our approved IRB.

**Fig. 1 Fig1:**
[figure not shown]
Adaptive implementation of school-based CBT study flow and timeline. Potential to benefit from facilitation is defined as ≥ 1 participating SPs delivering < 3 cognitive behavioral therapy (CBT) components to < 10 students or school professionals (SPs) reporting, on average, > 2 barriers to CBT uptake

### Setting

The study will take place in high schools across Michigan’s 83 counties, with CBT delivered by existing SPs for students with depression and anxiety. The REP (which includes CBT manual package, training, and technical support for SPs), coaching, and facilitation implementation strategies will be provided through the TRAILS program [31].

### Study design

Figure 1 details the four phases of this study over an 18-month period; the four phases are 3, 2, 10, and 3 months in duration, respectively.

The run-in phase involves deployment of the REP implementation strategy (CBT manual package, training, and technical assistance) and identification of schools, SPs, and potential students in need of CBT by SPs.

For phase 1, eligible schools are randomized with equal probability to continued REP only versus REP combined with coaching (REP+coaching). At the end of phase 1, schools are assessed to determine whether they would potentially benefit from facilitation.

During phase 2, schools that could benefit from facilitation [39] (see Additional file 1: Appendix 1) will be re-randomized in phase 2 with equal probability to continue their implementation strategy from Phase 1 (i.e., REP or REP+coaching) or to have their current strategy augmented with facilitation (i.e., REP+facilitation or REP+coaching+facilitation, respectively). The active elements of the coaching and facilitation strategies will be paused during the summer months (June–August 2019) when schools are not in session.

For phase 3, all implementation strategies will be discontinued. Outcomes will be collected longitudinally throughout all phases, from SPs up to 18 months after the baseline assessment and from students up to 15 months after their baseline assessment.

### Sites/schools

Over 200 SPs from up to 100 schools across the State of Michigan’s 900+ high schools will be recruited by study staff to participate in the study. Every attempt will be made to recruit at least one eligible school from each county in Michigan and to include rural as well as urban and suburban schools.

#### Site inclusion criteria

Schools will be eligible if theyAre a high school (grades 9–12) from a school district in one of the 83 counties in Michigan that has not previously participated in a TRAILS CBT training initiative.Are within a 2-h driving distance of a TRAILS coach (who are mental health professionals primarily working in community mental health clinics across Michigan).Agree to participate in data collection throughout the study duration.Identify at least one SP who is eligible and agrees to participate in study assessments throughout the study duration.Allow for SP(s) to deliver individual and/or group mental health support services on school grounds, yet outside of the general education classroom environment.

A school administrator who is a principal or other senior administrator at each participating school will be asked to provide data on building-wide sociodemographics and leadership support for evidence-based practices.

School professionals identified by schools are eligible if they areEmployed at a Michigan high schoolHave a background in clinical school social work, counseling, psychology, or similar fieldAble to read and understand English and comprehend study assessments

School professionals will be excluded if they have a significant illness or condition that precludes their participation in the implementation strategies, including the REP training and student identification process, coaching, or facilitation, or are unable to provide informed consent for participation in the study activities.

### Student eligibility and recruitment

As part of REP, SPs will be trained during the run-in phase to identify 10 eligible students in need of CBT. Because accurate case finding is critical to successful CBT implementation, training SPs on student identification is a core component of the REP implementation strategy [39] used in previous studies of implementation strategies [40, 50]. SPs will be taught through REP to recognize signs of depression and anxiety in students, using public domain screens (Patient Health Questionnaire 9 modified for teens [PHQ-9T] and generalized anxiety disorder [GAD]-7) [51].

Students are considered eligible if the SP determines they have at least one symptom of depression or anxiety that impacts their daily functioning and well-being. Students are considered ineligible as determined by the SP if they are (1) high school seniors (or would be graduating prior to any CBT sessions); (2) are unable to regularly attend school-delivered CBT skills groups; or (3) are unlikely to benefit from CBT skills groups due to cognitive or developmental disability, lack of English proficiency, or significant behavioral difficulties.

### Stratified randomizations

All randomization occurs at the school level. All study-eligible schools are randomized in phase 1 with equal probability to receive either REP or REP+coaching. In phase 2, schools with documented evidence of a need for additional implementation support based on predetermined criteria (see Additional file 1: Appendix 1) will be further randomized with equal probability to continue their phase 1 strategy (REP or REP+coaching) or to have their current strategy augmented with facilitation (REP+facilitation or REP+coaching+facilitation). To ensure balance across study arms, the first randomization will be stratified based on school size (> 500 or ≤ 500 students), location of school (rural or urban), percentage of students on free/reduced lunch program (≥ %50 or < 50%), and pre-randomization delivery of CBT (any sessions vs. none). The second randomization, among schools that might benefit from facilitation, will be stratified by size, location, and total number of CBT sessions provided in the 8 weeks post first randomization (top 50% vs. bottom 50% within REP or REP+coaching arm).

### Evidence-based practice (EBP) to be implemented

The EBP to be implemented is cognitive behavioral therapy (CBT) for youth with depression or anxiety [52–56]. Modular CBT—defined as individual components of CBT, delivered flexibly and responsively to presenting symptoms [47]—will be utilized in particular, due to its strong evidence base and advantages over other manualized protocols for school-based delivery [45, 49]. Modular CBT has been previously found in several studies to be associated with reduced depressive and anxiety symptoms when compared to usual care [44, 57], and among students in particular [48, 58]. CBT has also been delivered successfully for different racial and ethnic groups [8, 57], thus making it ideal for a statewide trial within schools [59, 60]. Core CBT components used in this study are based on previously established interventions [55, 61] and include psychoeducation, relaxation, instruction in identification and replacement of anxious or depressive thoughts, behavioral activation, creation of fear hierarchies, and exposure. Additional emphasis will be placed on active intervention techniques associated with improved engagement and clinical outcomes, such as agenda setting, modeling of skills, practice with feedback, and assignment of take-home practice activities [62].

### Implementation strategies and components

#### REP

Replicating Effective Programs (REP) [36] will be provided to all schools and is based on Rogers Diffusion Model [63] and social learning theory [64]. REP enhances EBP uptake by customizing interventions to fit the needs of specific settings through EBP packaging (tailoring of the modular CBT manual in user-friendly language), didactic training, and ongoing technical assistance provided by the TRAILS program. The package includes an overview of CBT core components, agendas describing how each component is delivered within a session, sample student screening forms, talking points for students, and suggestions for school-based delivery. REP training to be provided by TRAILS covers modular CBT core components including screening and identification of students. REP technical assistance consists of regular scheduled conference calls during which SPs may receive support from an expert CBT clinician and open access to an interactive website that provides additional resources (e.g., video demonstrations, case simulations) (Table 1).

**Table 1 Tab1:** Summary of implementation strategies across REP, REP+coaching (REP+C), REP+facilitation (REP+F), and REP+coaching+facilitation (REP+C/F)

Implementation component	REP	REP+C	REP+F	REP+C/F
Replicating Effective Programs (REP)	All sites	All sites randomized	All REP sites that might benefit from facilitation randomized	All REP+C sites that might benefit from facilitation randomized
Step 1: market CBT and disseminate CBT package: a. Recruit schools, disseminate information on CBT program (TRAILS), and R01 study b. Recruit SPs and require they identify 10 students for CBT c. Orient and train SPs to use web tool to track all CBT encounters c. Schedule SP CBT training and program CBT web tool d. Disseminate CBT package (manual + implementation guide) to school professionals (SPs). Implementation guide includes overview of CBT core components (e.g., cognitive restructuring, exposure), session agendas, sample screening forms, talking points, and additional resources.	♦	♦	♦	♦
Step 2: train SPs in CBT 1-day training on the evidence behind CBT and a step-by-step walk-through of core components. Cover common signs of depression and anxiety in students and utilization of public domain screens (e.g., PHQ9T, GAD7).	♦	♦	♦	♦
Step 3: as-needed program assistance and CBT uptake monitoring: bi-weekly conference calls held by REP specialists with an interactive website that provides additional resources (video, case simulations) and Q&A forum led by a REP/CBT expert to address questions regarding clinical content, use of the web tool, manualized materials, and school-based implementation.	♦	♦	♦	♦
Coaching (C)				
CBT expert (coach) attends with SP the CBT sessions delivered to identified students. Coaches will meet with SPs before and/or after each session to address any concerns, questions, or challenges to delivery. a. Weekly pre-session planning by phone or email, direction to appropriate materials and resources, and role-play practice of specific treatment elements b. In vivo modeling of treatment skills during CBT group treatment sessions, observation of SPs’ treatment delivery, post-session discussion of strengths and areas for improvement, and practice of skills with feedback c. Didactic instruction/guided practice of specific skills as needed.		♦		♦
Facilitation (F)				
**S**tep 1: initiation and benchmarking: facilitator with expertise in CBT, implementation methods, education system, and use of EBPs in schools contacts each SP and holds a call with SP to review potential barriers and facilitators to CBT uptake, and set measurable goals for CBT uptake			♦	♦
Step 2: mentoring: facilitator and SP hold regular calls to develop rapport; provides guidance to SP on overcoming specific barriers to CBT uptake by aligning SP strengths with available influence at the school and needs of administrators. If needed, facilitator refers SP to REP TA.			♦	♦
Step 3: leveraging: Facilitator continues calls with SP and with SP reaches out to school administrators, identifies school/community priorities per administration input, and helps SP align CBT use/goals with these existing priorities. Facilitator helps SP summarize and describe added value of CBT to administrators and other school employees (e.g., consistency with other initiatives).			♦	♦
Step 4: ongoing marketing: facilitator, leadership, and SP summarize progress and develop sustainability plans.			♦	♦

*REP* Replicating Effective Programs, *CBT* cognitive behavior therapy, *SP* school professional, *PHQ-9T* Patient Health Questionnaire 9-item Survey for Teens, *GAD-7* Generalized Anxiety Disorder 7-item survey, *EBP* evidence-based practice

♦ represents the presence of the specific implementation component under each implementation strategy to be provided in the study

#### Coaching

The coaching implementation strategy (Table 2) is provided by TRAILS clinicians and is derived from the school-based Positive Behavior Interventions and Supports (PBIS) model of coaching for individual development [65]. Coaching uses a CBT training expert to attend in person to observe group sessions led by the SPs, provide live feedback [66, 67], and model the use of core CBT elements to improve SP competence [65, 68–72]. All SPs from schools randomized to coaching in phase 1 will receive weekly visits from a CBT coach for a minimum of 12 weeks, which will occur in the context of the SPs weekly CBT group. After 12 weeks of on-site coaching, SPs are evaluated on their CBT skill delivery through a short objective competency quiz. SPs deemed to need a full second round of coaching based will receive another full 12 weeks of coaching.

**Table 2 Tab2:** Fidelity checklist summary for REP, coaching, and facilitation components

Implementation step	Specific implementation tasks	Date completed	Summary of fidelity measure for each component
REP	Step 1: identify schools and SPs, market CBT program		# SP names and contacts, marketing reach (# web hits)
	Step 1: DM disseminates SP and school administrator baseline surveys		# completed surveys
	Step 1: TS orients and trains SPs to use web tool to track all CBT encounters		# SPs at schools receiving package, # website visits
	AN randomizes eligible sites to REP or REP+coaching—phase 1		Complete phase 1 randomization
	Step 2: TS holds training (1 day)		# SPs trained
	Step 2: DM receives list of 10 students/SP		# students listed at each site
	Step 3: TS with TA begin virtual CBT technical assistance phase via regular calls		Call date with SPs, # CBT sessions/site
	Step 3: DM monitors SP uptake of CBT at schools via web tool		# students identified at each school, # CBT sessions
	Step 3: DM starts student assessments		# student assessments completed
	Step 3: TA disseminates school-specific uptake monthly report, eligibility survey		# monthly reports disseminated to each school
	AN determines if site would benefit from facilitation		
	AN randomizes sites that might benefit to add facilitation or not—phase 2		Complete phase 2 randomization for schools that might benefit from facilitation
	Step 3: TA holds as-needed calls with SPs upon request regular conference calls		# conference calls held and attendance
	Step 3: TA sends out regular newsletter highlighting CBT success stories		# newsletters disseminated
Coaching	Coaching fidelity checklist (TRAILS)		
	Step 1: Pre-CBT session to focus on priorities in CBT session		Coach communicates with SP prior to session to identify 2–3 session priorities, provides resources
	Step 2: During CBT session, feedback on session quality		Coach attends student skills group session with SP Role played a skill during session and models skill delivery
			Coach documents if any session components are incomplete/insufficient, and during session models proper delivery during group
			Coach provides 1–2 session strengths and 1–2 session weaknesses to SP, via written or oral feedback
			Coach provides 1–2 suggestions for improvement in delivery, via written or oral feedback, on either CBT skill or overall presentation of group format
	Step 3: Post-CBT-session, preview of upcoming sessions		Coach previews upcoming session goal with SP, provides additional guidance on delivery based on strengths/weaknesses
Facilitation	Step 1 (initiating and benchmarking): facilitator initiates SP calls, identifies barriers, facilitators to CBT implementation		# calls completed with SPs, # minutes/call
	Step 1: facilitator and SP agree on specific uptake goal (e.g., % students completing six sessions)		Facilitator records each site-specific goal, and if met in 6 months
	Step 2 (mentoring): facilitator continues regular calls w/SP, IDs strengths, and influence points; identifies school administrator priorities and additional school champions		Facilitator lists SP’s strengths, linkages to points of influence, school priorities, and champions
	Step 2: facilitator assists SP in aligning strengths/influence with specific CBT uptake goals and advises on aligning strengths to enhance implementation		Facilitator completes action plan linking strengths
	Step 3 (leveraging): facilitator consults with SP’s coach and SP (facilitation + coach arm only) and provides guidance on mitigating barriers to uptake		# consultations with coach
	Step 3: facilitator holds monthly consultation meeting with study staff, coach consultation team		# meetings, minutes created by facilitator
	Step 3: facilitator helps SP summarize and present added value of CBT to administrators		Facilitator records examples of CBT added value
	Step 4 (ongoing marketing): facilitator/SP develop CBT sustainability plan and present to site leadership		Facilitator/SP completes sustainability plan
	Step 4: facilitator refers SPs to additional resources including REP TA		# referrals facilitation made for each site to TA

*TA REP* technical assistant, *TS REP* training specialist, *CC* coach coordinator, *AN* analyst, *DM* database manager, *RA* research assistant

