## Methods/Design

### Aims and objectives

#### Primary study aim

The primary aim of this study is to compare the effectiveness of an adaptive implementation intervention on CBT delivery among schools versus REP alone (the control). The adaptive intervention provides schools with REP + coaching from the start and subsequently augments with facilitation for schools needing additional assistance. The primary outcome is the total number of CBT sessions delivered to students by SPs over an 18-month period. Number of CBT sessions is defined further below, and includes group and individual sessions delivered to students.

Specific CBT component delivery and whether delivery of individual or group sessions were brief (< 15 min) or full-length (≥ 15 min) will also be tracked and examined as secondary outcomes. As an exploratory outcome for this primary aim, we will also examine change in student mental health symptoms among students over the study period.

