### Trial status

The study has not started as of August 2018. In the run-in phase (October 2018–January 2019), all eligible SPs will receive Replicating Effective Programs (REP) components, including a 1-day didactic training in CBT in mid-January of 2019. The first randomization will occur in late January 2019.

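### Table 2 starts the student surveys after the first randomization, in conflict with the text on neighbouring steps, and no passage shown requires the student baseline before allocation

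*Protocol article*

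**What the plan says.** All references are to the protocol article.

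- **Table 2 (fidelity checklist, REP rows).** SP and administrator baseline surveys are a Step 1 task. Next but one comes "AN randomizes eligible sites to REP or REP+coaching—phase 1". Below that come "Step 2: TS holds training (1 day", then "Step 2: DM receives list of 10 students/SP", then "Step 3: TS with TA begin virtual CBT technical assistance phase via regular calls", then monitoring of uptake, and only then "Step 3: DM starts student assessments".
- **Study design.** The run-in deploys REP, including technical assistance, and covers "identification of schools, SPs, and potential students in need of CBT by SPs". The four phases last 3, 2, 10 and 3 months. Students are followed for up to 15 months from their baseline.
- **Table 3.** PHQ-9T and GAD-7 are collected at months 3, 6, 12 and 18, with no earlier value.
- **Trial status.** The one-day training is in mid-January 2019, within the run-in. Then: "The first randomization will occur in late January 2019".
- **Analyses.** Student outcomes are analysed only in schools where at least one SP supplied a list of students before the first randomization. Nothing is said about the date of the students' first survey.
- **Measures and Student outcomes.** SPs facilitate the student surveys, which are completed electronically.
- **Primary study aim.** As an exploratory outcome, "we will also examine change in student mental health symptoms among students over the study period".

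**The concern.** A change in symptoms has a clean randomized interpretation only if the starting value could not have been affected by allocation. Here the allocation is by school, and the SP who facilitates the survey knows it: in coached schools a coach attends the SP's CBT group weekly. Coaching is meant to increase CBT delivery. If first surveys are taken after allocation, those in coached schools may more often follow the first sessions. Any early improvement would then sit in the baseline and be subtracted from the change in that arm more than in the other.

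The same scores feed the depression- and anxiety-free days in the cost-effectiveness ratios (Exploratory aims, under Analyses), so the error would carry over. The rule on student lists does not close this gap. It guards against students being listed after allocation, but it does not date the measurement.

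**Working it through.** **1. Where the student baseline falls.** Inputs are from Study design and Table 3.

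- Total length: 3 + 2 + 10 + 3 = 18 months.
- Student baseline: 18 − 15 = month 3, which agrees with the first PHQ-9T/GAD-7 in Table 3.
- End of run-in: month 3, the nominal time of the first randomization.

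So the schedule puts the student baseline on the boundary and does not say which side.

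**2. Order of tasks in Table 2 against the text.**

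| Task | Row among REP tasks in Table 2 | Elsewhere in the article |
|---|---|---|
| SP and administrator baseline surveys | 2, before randomization | Table 3: baseline; consistent |
| Phase 1 randomization | 4 | Trial status: late January 2019 |
| Training | 5, after randomization | Trial status: mid-January 2019, before randomization; contradicts |
| Student list received | 6, after randomization | Analyses: list expected before randomization; sits badly |
| Technical assistance begins | 7, after randomization | Study design: part of the run-in; sits badly |
| Uptake monitoring | 8, after randomization | No date given |
| Student assessments start | 9, after randomization | Table 3 and Study design: month 3, side not stated |

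Moving randomization below training and listing, to agree with Trial status and Analyses, still leaves the start of student assessments unresolved. It could fall just before or just after allocation.

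**3. How a late baseline would act.** Let f be the share of first surveys in an arm taken after early CBT, and d the early improvement already present in them. In a simple change-score comparison the between-arm contrast shifts by

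−(f_adaptive × d_adaptive − f_REP × d_REP).

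The shift is zero if the two products are equal. It reduces the apparent benefit of the adaptive intervention if its product is larger. The documents give none of the four inputs.

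As an illustration only, take d_adaptive as one quarter of the final effect, f_adaptive from 0.2 to 0.8, and no early effect under REP. Then 0.2 × 0.25 = 5% and 0.8 × 0.25 = 20% of the final effect would be lost. The REP assumption pushes these figures up, because REP-only SPs are also trained and supported to deliver CBT.

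**4. What is not touched.** The only sample-size figure concerns SP-reported CBT sessions, and it reproduces. With D = 0.53, ICC = 0.03, 2 SPs per school and response rates of 10% and 50%:

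- Design effect: 1 + (2 − 1) × 0.03 = 1.03.
- Weighting factor: 1 + (0.90 + 0.50)/2 = 1.70.
- Schools needed: 4 × (1.960 + 0.842)² / 0.53² × 1.03 × 1.70 / 2 = 97.9, so 98.
- Power with 100 schools: 80.8%.

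None of this uses the student surveys.

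**The case against.** The strongest objection is that Table 2 is a fidelity checklist, not a visit schedule. Its date column is blank and its row order is demonstrably wrong on training. A Step 3 label does not mean after allocation either, since technical assistance, also Step 3, belongs to the run-in. This stands. A reader might infer from Table 2 that the baseline **is** taken after randomization; the documents do not establish that. It would also be inconsistent to take Trial status as right on training and Table 2 as right on student assessments.

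Other inferences that the documents do not support:

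- **That SPs choose the survey date.** No passage says so. Table 2 has the database manager start the assessments, and Table 3 gives fixed months. SPs only facilitate.
- **That support given before baseline is in itself a bias.** REP goes to every school from the run-in, and CBT before randomization is foreseen and used as a stratification factor. Neither differs by arm; only the coaching route could.
- **That the surveys cannot be fitted in before allocation.** About 200 SPs × 10 students is up to 2,000 surveys, and mid- to late January is roughly one to two weeks. But that is about 10 electronic surveys per SP, done in parallel, and Student outcomes allows students to be identified before training.

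Figure 1 and the appendices, including the detailed analysis plan, are not shown, and they may settle the order or the handling of late surveys. That limits what can be said about absence. It does not remove the contradiction within the article, and an analysis plan cannot recover a pre-allocation value that was never collected.

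**Conclusion.** The point holds as a reconciliation matter with a possible bias behind it. The article's one explicit task sequence starts student assessments after the first randomization and after uptake monitoring, while SP and administrator baselines come before. That sequence conflicts with Trial status on training and fits poorly with Analyses on student lists. The schedule puts the student baseline at month 3, exactly on the boundary, and no passage shown requires it before allocation.

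Whether bias results depends on three conditions: that surveys are in fact taken after allocation, that CBT starts earlier or more often in coached schools, and that symptoms respond early. Its size cannot be derived from the documents. The 5–20% range is an illustration with assumed inputs, not an estimate.

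The reach is limited to change in student symptoms and the cost-effectiveness analysis based on it. Primary study aim, Exploratory aims and Table 3 class these as exploratory, although the Abstract mentions student mental health within the primary aim. The primary outcome and the sample size stand.

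**What to change.** 1. Reorder the REP rows of Table 2 to agree with Trial status (training before randomization) and Analyses (student lists before randomization).
2. State in Table 3 or Student outcomes that each listed student's baseline survey is completed before the school's allocation is disclosed. Show this in Table 2 as a task above the randomization row.
3. Use the electronic surveys' time-stamps to date each first survey against disclosure. Flag a first survey after disclosure and do not use it as a pre-allocation baseline: treat it as follow-up, with the baseline missing under the planned multiple imputation. Missing data names only primary and secondary analyses, so say that imputation extends to the exploratory student outcomes.

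The cost is low. Trial status reports that the study had not started as of August 2018, so this is a change of wording and use of survey records. The downside is a short delay in disclosing allocation at some schools, or some students with an imputed baseline.
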